### Standard of care control condition

For Stage 1 (PrEP linkage/uptake), the SOC condition consists of the provision of resources including information about oral and injectable PrEP (what they are, how they work, their efficacy), how to pay for PrEP with or without insurance, and a list of local resources for mental and sexual health, primary care, sexual assault, domestic violence, substance use, and HIV/STI care and prevention. Irrespective of the study condition, if they attend a PrEP appointment, participants can be prescribed PrEP at the discretion and following the protocol of the prescribing clinician.

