#### Co-primary outcome measures

PrEP uptake is measured via confirmation of medical and pharmacy records. We obtain a release of medical information from participants at the Stage 2 baseline. Study staff follow up with PrEP providers (to verify clinical PrEP eligibility and visit attendance) and pharmacies (to determine whether prescriptions for TDF/FTC or TAF/FTC were filled and dates when filled to assess time to initiation). Study staff also request at each follow-up assessment that participants show their pill bottles to confirm that the prescription was picked up.

For those who initiate PrEP, longer-term (past month) adherence is assessed at 4-, 8, and 12-month visits by collecting hair samples to test for detectable levels of TDF/FTC or TAF/FTC. Samples are ~ 50–100, 1-2 mm-long hair strands cut with scissors. As in our other studies, samples are stored and shipped to the University of California San Francisco Hair Analysis Lab (HAL) for analysis. Although this method was highly feasible and acceptable in our pilot (> 95% provided samples) [17], participants refusing to provide hair (or those without sufficient hair) can continue to participate. Self-reported adherence supplements biological monitoring at all major assessments. In line with our prior trials and available evidence regarding the validity and reliability of self-reported adherence assessments, participants are asked to rate their adherence frequency (e.g., “all the time”) and report missed doses [23]. Additionally, retention in PrEP care is assessed based on the number of PrEP visits attended over 12 months of follow-up (after initial appointment, 2 + appointments will be considered optimal retention).

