#### Secondary outcome

PrEP persistence is assessed using pharmacy and medical records to confirm prescription refill maintenance. As per Coy et al., PrEP persistence is defined as having ≥ 16 days of PrEP medication filled per 30-day period for at least three-quarters of those months from initiation to study completion (~ 9 months) [24].

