### Statistical analyses

#### Aim 1

The primary analysis for Stage 1 will compare PrEP initiation (operationalized as having been prescribed PrEP medication) by two months post-Stage 1 randomization between the study arms. For Stage 2, the primary analysis will compare adherence (operationalized by detectable PrEP drug level in hair) at the 4-, 8-, and 12-month visits between study arms. Moreover, group differences in the number of PrEP clinic appointments kept and changes in self-reported adherence and sexual behavior adjustment will also be compared. All analyses will use two-tailed significance tests, with significance at alpha = 0.05. For each analysis, we will use generalized linear models (GLMs) with properly chosen link functions to analyze longitudinal data. The GLMs will be estimated using generalized estimating equations with robust standard error estimates (GEE), which provides an extension of regression analysis to the case of correlated or repeated observations and allows for the inclusion of both categorical and count dependent variables, as well as for appropriate modeling of covariance structures when observations are correlated across time [29, 30]. We will follow an intent-to-treat model, analyzing participants according to the study arm to which they were assigned, regardless of fidelity to the assigned group. Participants in Stage 2 who miss two or more sessions will be categorized as “non-completers” and analyzed secondarily in sensitivity analyses (dose-response relationship).

#### Aim 2

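### Stage 1 uptake and Stage 2 entry are defined for PrEP of any kind, but the pharmacy check, pill-bottle check and hair assay recognise only TDF/FTC or TAF/FTC, so injectable users have no consistent classification on the co-primary outcomes

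*Protocol article*

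**What the plan says.** All references are to the protocol article.

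**Where the scope is open**
- *Standard of care control condition*: Stage 1 controls receive "information about oral and injectable PrEP (what they are, how they work, their efficacy"), together with advice on paying for PrEP. In either arm, "participants can be prescribed PrEP at the discretion and following the protocol of the prescribing clinician". The article states no restriction to oral products.
- *Statistical analyses, Aim 1*: the Stage 1 outcome is "PrEP initiation (operationalized as having been prescribed PrEP medication) by two months post-Stage 1 randomization". No product is named. The Abstract, which defines uptake by a filled prescription, names none either.
- *Timing of assessments*: a man enters Stage 2 once a PrEP prescription in his name has been verified, again with no product named. A man who does not initiate has his last assessment at 2 months.
- *Co-primary outcome measures*, opening sentence: "PrEP uptake is measured via confirmation of medical and pharmacy records".

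**Where the scope is narrow**
- *Co-primary outcome measures*, uptake: staff contact pharmacies "to determine whether prescriptions for TDF/FTC or TAF/FTC were filled and dates when filled to assess time to initiation", and at follow-up ask that "participants show their pill bottles to confirm that the prescription was picked up".
- *Co-primary outcome measures*, adherence: this is assessed by "collecting hair samples to test for detectable levels of TDF/FTC or TAF/FTC". The Abstract names tenofovir in hair.
- *Secondary outcome*: persistence is a count of "days of PrEP medication filled per 30-day period", from pharmacy and medical records.

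**The concern.** The article brings injectable PrEP into the trial and then describes checks that can only see oral tenofovir products. It does not say how a man on injectable PrEP is classified for uptake, whether he is re-randomised, or how his hair result is read.

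Two things are at stake. In Stage 1, the same man can be an initiator or not depending on which section is followed. In Stage 2, an injectable user admitted on his prescription can only give an undetectable hair result. Aim 1 defines adherence as detectable drug in hair, so he would count as non-adherent although he may be fully covered. That misclassification is unrelated to the counselling and text messages under test, so it dilutes the comparison on which the trial's power is based.

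**Working it through.** **1. One injectable starter under each section.** I assume that injectable PrEP is a product other than TDF/FTC or TAF/FTC. The article implies this by separating oral from injectable PrEP, but does not state it.

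| Section | Criterion | Injectable starter |
|---|---|---|
| Statistical analyses, Aim 1 | PrEP prescribed by 2 months | Initiator |
| Timing of assessments | Verified PrEP prescription | Enters Stage 2 |
| Abstract | Prescription filled, no product named | Not excluded |
| Co-primary measures, pharmacy check | Fill of TDF/FTC or TAF/FTC | Fails |
| Co-primary measures, pill bottle | Bottle shown | Cannot be met |
| Co-primary measures, hair | TDF/FTC or TAF/FTC detectable | Cannot be met |
| Secondary outcome | Days filled per 30-day period | No product named, but days filled fits injections poorly |

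A man who switches from oral to injectable PrEP during Stage 2 meets the same hair problem once his oral use lies outside the past month that the assay covers.

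**2. The plan's own power.** *Sample size calculations* gives d = 0.54, two-sided alpha 0.05, 63 completers per arm, and power above 80% at four months. A two-sample t-test gives 85.3% (normal approximation 85.8%), so the stated figure reproduces. At d = 0.54, 80% power needs 54.8 per arm.

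**3. Stage 2 sensitivity.** Let f be the share of Stage 2 men on injectable PrEP, equal in both arms. The article gives no value; 5% to 30% is an assumed range.
- Scored undetectable: a fraction f scores zero in both arms, so the difference shrinks to d × (1 − f), with the SD held fixed and n = 63.
- Excluded from the hair analysis: d stays at 0.54 and n becomes 63 × (1 − f).

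| f | d if scored undetectable | Power | n per arm if excluded | Power |
|---|---|---|---|---|
| 0 | 0.540 | 85.3% | 63 | 85.3% |
| 5% | 0.513 | 81.5% | 59.9 | 83.4% |
| 10% | 0.486 | 77.2% | 56.7 | 81.3% |
| 20% | 0.432 | 67.2% | 50.4 | 76.6% |
| 30% | 0.378 | 55.8% | 44.1 | 70.8% |

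Power reaches 80% at d = 0.503 with 63 per arm, so the margin is used up at f = 1 − 0.503/0.54 = 6.8% if these men are scored undetectable. Under exclusion it is used up at f = 1 − 54.8/63 = 13.0%.

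**4. Check on the binary scale.** The Aim 1 outcome is detectability, so I repeated the first case with proportions. An assumed control rate of 40% and an arcsine effect size of 0.54 give 66.6% in the intervention arm. Multiplying both rates by (1 − f) gives power of 85.8% (f = 0), 81.8% (5%), 77.4% (10%), 68.0% (20%) and 58.1% (30%). The picture is the same.

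**5. Stage 1.** With 20% attrition, 63/0.8 = 78.75, so 79 per arm enter Stage 2. That is 158 of 500, an implied uptake of 31.6%. The Background reports a two- to threefold pilot ratio, which gives 21.1% vs 42.1%, or 15.8% vs 47.4%. If 30% of starters were missed in each arm, these become 14.7% vs 29.5%, or 11.1% vs 33.2%, and power with 250 per arm is still about 98% or more. Equal undercounting therefore does little harm to Stage 1 power.

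Unequal undercounting would bias the comparison. As a purely hypothetical case, take true uptake of 25% in both arms, with injectable shares of 20% in control and 5% in intervention. Counting oral fills only gives 0.25 × 0.80 = 20.0% against 0.25 × 0.95 = 23.75%, an apparent difference with no true effect.

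**The case against.** A reader might infer that injectable users are scored as failures on both co-primary outcomes. The article does not support that. The Aim 1 definition, the Abstract and the Stage 2 entry rule are product-neutral, and the pharmacy clause can be read as a description of what staff ask rather than as the endpoint. A man classed as a non-initiator leaves at 2 months and has no hair outcome. A man admitted to Stage 2 on his prescription has met the Aim 1 uptake definition. Failing both would require the open entry rule to be combined with the strict fill rule for uptake, and the article does not state that combination.

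A reader might also infer a bias toward the intervention in Stage 1, because injectable information is described only for the control package. The article does not show this. Case managers in the intervention arm explain what PrEP is, and a condensed description that names no product does not establish that they leave injectables out. Nor does giving information amount to promoting a product.

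Three further points are fair. The Background describes PrEP as a daily pill, which suggests that an oral trial was intended. The persistence rule names no product and also draws on medical records. The handling of non-oral products may be set out in a full protocol or SAP that is not shown.

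These points narrow the concern but do not remove it. The article itself names the drugs in the measures and leaves the product open in the definitions, so the contradiction is in the text. In Stage 2, following the stated entry rule and assay literally misclassifies covered men. If entry were instead governed by the oral fill check, only later switchers would be affected, but the article does not say that it is.

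**Conclusion.** The concern holds as an inconsistency of product scope, with a definite consequence in Stage 2. On uptake, the classification of an injectable starter depends on which section is followed. On adherence, an injectable user or switcher cannot be shown to be adherent by the hair assay, and no rule for him is stated.

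The size depends on the unknown injectable share. If such men are scored undetectable, power for the four-month comparison falls from about 85% to about 82%, 77%, 67% and 56% at shares of 5%, 10%, 20% and 30%; the claimed power above 80% survives at 5% but not at 10%. If they are excluded, power is about 83% to 71% over the same range. These figures assume equal shares in the two arms, 63 analysed per arm before exclusions, and an effect in oral users equal to the planned d = 0.54. Stage 1 power is not threatened under the uptake rates derived above. Differential undercounting in Stage 1 is possible but not shown.

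**What to change.** Reconcile the Abstract, Timing of assessments, Standard of care control condition, Co-primary outcome measures, Secondary outcome and Statistical analyses so that they share one product scope.

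- **Uptake.** Use one definition in both arms: a verified start of any PrEP product by two months, with oral fills verified from pharmacies and injections from medical records.
- **Adherence.** State that injectable users and switchers in Stage 2 are not scored non-adherent on undetectable hair. Either limit Stage 2 entry and the hair endpoint to men starting oral tenofovir-based PrEP, or classify injectable users at each visit as covered or not covered from medical records. The first option still needs a rule for later switchers.
- **Persistence.** Add a matching rule for injectable users in place of days filled.

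Most of this is wording, and recruitment is described as ongoing, so the rules can be set before outcomes are analysed. It is not free. The medical release is obtained at Stage 2 baseline, and *Measures* places record review in the second stage, so verifying injectable starts for Stage 1 may require an earlier release. Slightly fewer men may contribute to the hair analysis; under exclusion, the margin above 80% power is used up at a share of about 13%.

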#### Secondary outcome

PrEP persistence is assessed using pharmacy and medical records to confirm prescription refill maintenance. As per Coy et al., PrEP persistence is defined as having ≥ 16 days of PrEP medication filled per 30-day period for at least three-quarters of those months from initiation to study completion (~ 9 months) [24].

#### Conceptual mediators

Guided by our formative work and our conceptual model [14, 15, 17, 21, 22, 25, 26], variables hypothesized to be mediators of the intervention effect, including HIV and PrEP adherence information, PrEP motivation, and behavioral skills, are measured at each major assessment. Assessments are based on adaptations of validated scales [27, 28] and were used in our pilot study [17].

#### Hypothesized moderators

According to our model, the following moderators and descriptive measures are assessed: Socio-demographics (age, sexual identity, race/ethnicity), psychosocial (depressive and anxiety symptoms, trauma and abuse), substance use, and sex work disclosure.

### Statistical analyses

#### Aim 1

The primary analysis for Stage 1 will compare PrEP initiation (operationalized as having been prescribed PrEP medication) by two months post-Stage 1 randomization between the study arms. For Stage 2, the primary analysis will compare adherence (operationalized by detectable PrEP drug level in hair) at the 4-, 8-, and 12-month visits between study arms. Moreover, group differences in the number of PrEP clinic appointments kept and changes in self-reported adherence and sexual behavior adjustment will also be compared. All analyses will use two-tailed significance tests, with significance at alpha = 0.05. For each analysis, we will use generalized linear models (GLMs) with properly chosen link functions to analyze longitudinal data. The GLMs will be estimated using generalized estimating equations with robust standard error estimates (GEE), which provides an extension of regression analysis to the case of correlated or repeated observations and allows for the inclusion of both categorical and count dependent variables, as well as for appropriate modeling of covariance structures when observations are correlated across time [29, 30]. We will follow an intent-to-treat model, analyzing participants according to the study arm to which they were assigned, regardless of fidelity to the assigned group. Participants in Stage 2 who miss two or more sessions will be categorized as “non-completers” and analyzed secondarily in sensitivity analyses (dose-response relationship).

#### Aim 2

For mediation analyses, path analysis will be conducted using structural equation modeling (SEM) to determine whether the effect of the intervention on uptake and/or adherence was through the hypothesized mediators (e.g., increased PrEP knowledge, increased problem-solving skills to take PrEP, increased self-efficacy for PrEP adherence). SEM allows for the simultaneous estimation of total, direct, mediated, and indirect effects of a causal variable (i.e., the intervention) on the outcome (i.e., adherence) through a set of mediator variables [31]. SEM can handle outcomes and mediators with a variety of distributions (including Gaussian, Poisson, and Binomial). Inferences for indirect effects will be estimated using bootstrapped confidence intervals [32]. For effect modification (moderation) analyses, we will add interaction terms one by one for the intervention condition and the potential moderators (e.g., race, substance use at baseline, psychosocial factors; see Measures). Significant or large interaction terms suggest that intervention effects differ by subgroups of the moderators.

#### Aim 3

For the cost-effectiveness analysis, the costs of providing this intervention relative to the SOC arm will be estimated based on detailed records of resources required to implement the intervention from an organizational perspective, including the average personnel cost per participant for each intervention arm. The lifetime treatment cost of an HIV infection will be used as a conservative threshold value for the cost of averting one infection. The intervention will then be deemed cost-saving if it costs less than this threshold.

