**Methods:**

In this protocol paper, we describe the design and procedures for a National Institute of Health-funded, randomized controlled trial testing the efficacy of “PrEPare for Work,”— a theory-based, manualized PrEP uptake and adherence intervention for MSW — using a 2-stage randomization design. Stage 1: MSWs are equally randomized to receive either the “PrEPare for Work Stage 1 intervention” (strength-based case management and facilitated PrEP linkage) or Standard of Care (SOC) to evaluate successful PrEP uptake (prescription filled) within two months post-randomization. Stage 2: Those who initiate PrEP are then equally re-randomized to receive either the “PrEPare for Work Stage 2 intervention” (1-on-1 skills training, problem-solving, and motivational interviewing adherence counseling and personalized, daily text message reminders) or SOC to assess adherence (Tenofovir concentrations in hair) over 12 months of follow up. Planned analyses will examine intervention efficacy, specific conceptual mediators, and hypothesized moderators.

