While MSWs face multifaceted challenges to optimal adherence [12, 17, 18], developing and testing an intervention that recognizes and provides strategies to overcome such barriers and implement facilitators to PrEP uptake and adherence among MSWs is necessary to ensure maximum PrEP effectiveness. Efficacious ART adherence interventions for individuals living with HIV can be used as a starting point for addressing these unique challenges. One such intervention, Life-Steps, is an efficacious minimal-treatment behavioral intervention for adherence, which is conducive to adaptation [19–21]. It is based on Social Cognitive Therapy (SCT) and incorporates general principles of Cognitive-Behavioral Therapy (CBT) and Motivational Interviewing (MI) [17, 19–22]. The hypothesized mechanism of action is as follows: the intervention will help MSWs improve motivation, self-regulation, problem-solving skills, and strategies to take medications — all of which are strongly related to adherence and are key constructs of SCT [17, 19–22]. Using a staged intervention approach, we conducted extensive qualitative work to inform the adaptation. We then fielded a pilot RCT of the newly developed intervention to SOC [17]. In addition to demonstrating the feasibility and acceptability of the intervention, we found that participants randomized to “PrEPare for Work” SBCM were two to three times more likely than those in the SOC to attend an initial PrEP appointment, receive a PrEP prescription, and initiate PrEP. Additionally, individuals randomized to receive the “PrEPare for Work” Adherence Counseling intervention were nearly twice as likely to have prevention-effective adherence (measured via hair samples) compared to those in the SOC arm. However, this finding did not reach statistical significance due to insufficient power.

The current paper describes the protocol for a full-scale, multi-site RCT to determine the efficacy of the intervention to increase PrEP initiation and adherence, to examine hypothesized mediators and moderators of the intervention, and, if efficacious, to estimate the cost-effectiveness of the intervention to reduce HIV transmission among MSWs.

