### Timing of assessments

See Fig. 2 for details. Stage 1 has up to 3 major assessment points: Stage 1 Baseline (pre-randomization) and Post Stage 1 Assessments (at 1- and 2-months or at PrEP initiation, whichever occurs first). Participants who initiate PrEP (confirmed by a verified PrEP prescription in the participant’s name) complete the Stage 2 Baseline instead of the Stage 1 follow-up assessment. For participants who do not initiate PrEP, the 2-month follow-up is the final research assessment.

Stage 2 has four major assessment points: Stage 2 Baseline (pre-randomization), acute follow-up (4 months), and longer-term follow-ups (8 and 12 months). At each Stage 2 assessment, PrEP adherence is assessed via self-report; at 4-, 8-, and 12-month visits, a hair sample is collected to measure PrEP drug level in hair (long-term adherence). At the Stage 2 Baseline visit, a medical release is completed to obtain specific clinical indicators and associated HIV/STI testing results throughout the study period. At the 4- and 12-month visits, participants complete a self-collected HIV test and a urogenital (urine) test for chlamydia and gonorrhea. At all major assessments, participants complete a self-report battery, which includes secondary outcomes, a comprehensive psychosocial assessment of moderating factors, and potential mediators of the intervention.

Assessments are not blinded; however, only research staff who do not deliver intervention content administer follow-up assessments to reduce social desirability bias. Moreover, study staff use standardized survey instruments and are instructed on how to avoid bias in survey administration. Participants receive compensation for all study visits and may complete portions of study assessments remotely via a HIPAA-secured Zoom platform if desired. Between major assessments, check-ins (by phone or in-person) to support retention are incentivized.

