### Sample size calculations

The primary power analysis is based on the acute PrEP adherence outcome (differences between the intervention and control conditions from our “PrEPare for Work” pilot RCT), which demonstrated a meaningful but non-significant difference in PrEP adherence between the intervention and control groups from baseline to follow-up (effect size: 0.54) [17]. Therefore, the present study is powered to detect an effect size of d = 0.54 using a two-sided alpha = 0.05. Group sizes of 63 completers per arm (experimental intervention and the standard of care comparison), which assume 20% attrition in Stage 2, result in greater than 80% power in adherence at four months in a pair-wise comparison. Assuming similar rates of uptake and attrition to the pilot study, 250 individuals per arm are required for randomization.

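### The Stage 2 co-primary outcome is given both as drug concentration in hair and as detectable drug; the yes/no version cannot grade adherence and does not fit the standardised effect used for power

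*Protocol article*

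**What the plan says.** The protocol article describes the Stage 2 hair outcome in two ways.

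- **As a quantity.** The abstract says participants are re-randomised "to assess adherence (Tenofovir concentrations in hair) over 12 months of follow up". Timing of assessments says that at 4, 8 and 12 months "a hair sample is collected to measure PrEP drug level in hair (long-term adherence").
- **As detection.** Co-primary outcome measures describes "collecting hair samples to test for detectable levels of TDF/FTC or TAF/FTC". Statistical analyses, Aim 1, defines the primary comparison as "adherence (operationalized by detectable PrEP drug level in hair) at the 4-, 8-, and 12-month visits".

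Aim 1 leaves the link function of the GEE model open. No section gives an assay limit, a concentration cut-off or an expected detection rate.

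Two other statements bear on the choice. Background reports that pilot participants who received the adherence counselling "were nearly twice as likely to have prevention-effective adherence (measured via hair samples) compared to those in the SOC arm", a difference that was not significant. Sample size calculations says "the present study is powered to detect an effect size of d = 0.54 using a two-sided alpha = 0.05", with 63 completers per arm, 20% Stage 2 attrition and more than 80% power at four months. It attributes 0.54 to the pilot's adherence difference but does not say on which scale it was computed.

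**The concern.** Concentration and detectability are different outcomes. They need different models and answer different questions, and a reader cannot tell from the article which one will be tested.

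If Aim 1 is followed literally, there are two consequences.

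1. **Meaning.** A yes/no result treats everyone above the assay limit alike. Stage 2 offers counselling and daily text reminders to support taking PrEP every day, so much of the intended gain may lie above that limit. A positive result would show more men with some measurable drug. It would not show prevention-effective adherence, which is what the pilot signal concerned. The only graded adherence measure left would be self-report, which the article uses as a supplement.
2. **Power.** A d is a standardised mean difference. The stated power need not carry over to a comparison of two proportions.

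**Working it through.** **Inputs from Sample size calculations:** d = 0.54, two-sided alpha 0.05, 63 completers per arm, comparison at four months.

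**Assumed, because the documents do not give them:** the control-arm (SOC) detection rate p0, and the scale of 0.54.

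**Step 1. Reproduce the stated power.** For two means, power = Φ(d·√(n/2) − 1.96) = Φ(0.54 × √31.5 − 1.96) = Φ(3.03 − 1.96) = 0.858. The t-test gives 0.853. The claim of more than 80% is therefore correct for a standardised mean difference.

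**Step 2. Read 0.54 as a shift in concentration, then cut at detectability.** Two conversions give the intervention-arm rate p1:

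- Probit (normal latent scale): p1 = Φ(Φ⁻¹(p0) + 0.54).
- Logistic: odds ratio = exp(0.54 × π/√3) = 2.66, applied to the odds p0/(1 − p0).

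**Step 3. Read 0.54 as Cohen's h.** Here p1 = sin²(arcsin√p0 + 0.27).

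In Steps 2 and 3, power = Φ{(|p1 − p0| − 1.96·SE0)/SE1}, with SE0 = √(2·p̄(1 − p̄)/63), p̄ the mean of p0 and p1, and SE1 = √{[p0(1 − p0) + p1(1 − p1)]/63}.

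Example, probit with p0 = 0.80:

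- Φ⁻¹(0.80) = 0.842, and p1 = Φ(1.382) = 0.9165, a difference of 0.1165.
- SE0 = 0.0622 and SE1 = 0.0613.
- Power = Φ{(0.1165 − 0.1218)/0.0613} = Φ(−0.087) = 0.465.

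| SOC detectable (assumed) | Probit: p1, power | Logistic: p1, power | Cohen's h: p1, power |
|---|---|---|---|
| 40% | 61%, 67% | 64%, 78% | 67%, 86% |
| 50% | 71%, 66% | 73%, 75% | 76%, 86% |
| 70% | 86%, 56% | 86%, 59% | 91%, 84% |
| 80% | 92%, 47% | 91%, 45% | 96%, 82% |
| 90% | 97%, 31% | 96%, 26% | 99.7%, 70% |

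The 40% row is the best case for both concentration-shift conversions among the rates tried (20% to 95%), and neither reaches 80%. Under the probit conversion, 80% power would need 86 completers per arm at an SOC rate of 40%, 140 at 80% and 227 at 90%, against the 63 planned.

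**The case against.** The strongest reply is that the power loss depends on reading 0.54 as a concentration shift, which the article never says. The only pilot adherence result it describes is a proportion. If 0.54 is a standardised difference in proportions, the last column applies and the stated power largely survives. An illustrative split of 30% against 57% (ratio 1.9) gives h = 0.55, close to 0.54. The article writes d, so neither reading is established. The figures also cover one visit, and the GEE over three visits may recover some power. This objection stands, so the size of any loss is conditional.

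Some stronger readings are tempting but not supported:

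- **That there are three competing outcomes.** Prevention-effective adherence is reported for the pilot. The trial's own outcome has two descriptions.
- **That SOC detectability must be high because "Those who initiate PrEP are then equally re-randomized".** Initiation is confirmed by a verified prescription. Hair is taken 4 to 12 months later and reflects the past month, in a group the article describes as facing many barriers to adherence. Later discontinuation could make detectability informative.
- **That a near doubling is impossible once SOC detectability passes about 53% (1/1.9), so the design fails.** That ratio belongs to a different threshold, and the sample size does not use it.
- **That the test cannot tell occasional from regular pill-taking.** How little intake counts as detectable depends on an assay limit the article does not give. What follows from the dichotomy alone is that nobody above the limit is graded.

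Aim 1 could also be read as quantitative, since no link function is named. The co-primary measures wording favours the binary reading, and if concentration was meant, that wording still needs correcting. Modelling detail may sit in an SAP that is not shown. The operational definition of a co-primary outcome is stated here, however, and stated inconsistently.

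**Conclusion.** The point holds as an inconsistency in the definition of a co-primary outcome, with a mismatch between that outcome and the effect measure used for power. The sample size arithmetic is not wrong: 85% reproduces on a continuous scale. Under the literal Aim 1 endpoint, the four-month power with 63 per arm depends on two things the documents leave open:

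- **Concentration shift:** at most about 67% (probit) to 78% (logistic), about 45–47% if SOC detectability is 80%, and 26–31% if it is 90%.
- **Cohen's h:** above 80% up to an SOC detectability of about 80%, and about 70% at 90%.

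It would go too far to conclude that the trial is underpowered. The loss of grading above the assay limit does not depend on these assumptions. This should be fixed; confidence is moderate.

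**What to change.** Reconcile the abstract, Timing of assessments, Co-primary outcome measures and Statistical analyses on one Stage 2 primary outcome. The preferable choice is the quantitative hair concentration the abstract already names, for example on a log scale, with values below the assay limit treated as censored and the analysis accounting for TDF/FTC versus TAF/FTC. Report the pilot's prevention-effective definition as a binary secondary outcome, and detectability descriptively.

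State the scale on which the pilot effect of 0.54 was computed, and restate effect size and power on the scale of the chosen outcome. If detectability is kept as primary, give the expected rates in both arms and base power on them.

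The cost is mainly wording in the protocol and analysis plan, plus a restated power calculation. The hair samples are already planned at 4, 8 and 12 months. Recruitment was ongoing when the article was written, so the change could be made prospectively. The drawbacks are a headline less simple than a percentage and the need to handle two formulations.
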